# Protocol Summary

| **Study Title** | Neoadjuvant Long-course Chemoradiotherapy Followed by Immunotherapy for Locally Advanced Mid-low Rectal Cancer (NLCCRIT-LARC) |
| --- | --- |
| **Protocol No.** | NCT06493240 |
| **Version No** | 1.0 |
| **Sponsor** | Peking University People’s Hospital |
| **Principal Investigator** | [name] |
| **Participating sites** |  |
| **Research design** | A single-arm, open-label, phase II trial |
| **Study objective** | **Primary Objective**   - pathological complete response (pCR) rate   **Secondary Objectives**   - Sphincter preserving rate - Immune-related adverse event rate - Treatment-related adverse event rate - Incidence rate of surgical complications   **Exploratory Objectives**   - Longitudinal single-cell RNA-seq (scRNA-seq) and single-cell TCR-seq (scTCR-seq) of tumor tissue and matched peripheral blood to identify immune programs of response vs resistance |
| **Research subjects** | Previously untreated and confirmed by biopsy as rectal adenocarcinoma and MRI shows no distant metastasis, stage II/III (except T4b) |
| **Treatment Regimen** | The treatment regimen is 45-50.4Gy/25 fractions + 5-FU long-course radiotherapy and chemotherapy (5 times per week for 5 weeks, total dose of 45 to 50.4Gy). On the 15th day after the end of radiotherapy and chemotherapy, tumor tissue was biopsied and PD-1 monoclonal antibody (Sintilimab, 200mg, once a week, for 3 weeks) treatment was performed. The surgery was scheduled 8-12 weeks after radiotherapy completion. |
| **Inclusion Criteria** | Patients must meet all of the following inclusion criteria to be enrolled in the study:   1. Age: 18-80 years old 2. Previously untreated and confirmed by biopsy as rectal adenocarcinoma 3. MRI shows no distant metastasis, stage II/III (except T4b) 4. The lower edge of the tumor must be within 10 cm of the anal margin 5. ECOG performance status 0-2 6. Willing and able to comply with the research protocol 7. Agree to use blood and tissue samples for research 8. No history of anti-tumor treatment (such as radiotherapy, chemotherapy, immunotherapy, biology, herbal medicine, etc.) 9. No immune system diseases (such as systemic lupus erythematosus, rheumatoid arthritis, systemic vasculitis, scleroderma, pemphigus, dermatomyositis, mixed connective tissue disease, autoimmune hemolytic anemia, hyperthyroidism/hypothyroidism, ulcerative colitis, autoimmune hemolytic anemia, HIV infection, etc.) 10. No significant functional impairment of major organs (such as heart, lungs, liver, kidneys, etc.) 11. No jaundice or gastrointestinal obstruction; No acute/chronic infection 12. No obvious abnormalities in blood routine and biochemical tests: neutrophils≥1.5×109/L, hemoglobin≥80g/L, platelets≥100×109/L, total bilirubin≤1.5×ULN, ALT, AST≤2.5×ULN 13. No social or mental disorders 14. For women of childbearing age, the serological pregnancy test result needs to be negative, and effective contraception measures need to be taken within 60 days |
| **Exclusion criteria** | Patients with any of the following are not to be enrolled in the study:   1. Multiple types of cancer, or accompanied by tumors other than rectal cancer 2. Having received any anti-cancer treatment (surgery, medication, etc.) within the past 5 years 3. Recent history of major surgery 4. Conditions affecting the absorption of capecitabine through the gastrointestinal tract (such as inability to swallow, nausea, vomiting, chronic diarrhea, etc.) 5. Having any type of uncontrolled, severe, accompanying disease, allergic to any component of the study; estimated survival period≤5 years due to any reason 6. Preparing or previously having undergone organ or bone marrow transplantation 7. Receiving immunosuppressive or systemic hormone therapy within 1 month before inclusion for immunosuppression 8. For patients with a history of central nervous system diseases, the investigator needs to judge whether the clinical severity hinders signing the informed consent or affects the patient's oral medication compliance 9. Other situations/problems that may affect the research results or lead to the termination of the study (such as alcohol abuse, drug abuse, etc.) 10. Pregnant or lactating women, or women planning to conceive during treatment |
| **Statistical considerations** | The primary endpoint is pathological complete response (pCR). The trial is designed as a single-arm Phase II study with 80% power to detect an increase in the pCR rate from 5% (historical control for pMMR/MSS LARC after standard long-course radiotherapy) to 20% with a one-sided alpha of 0.05. Accounting for an anticipated 10% drop-out rate, a total of 30 patients will be enrolled. |
| **Period during which study was conducted** | First patient enrolled: 2023-01-01.  Planned enrollment duration: approximately 24 months to accrue ~30 patients.  Planned follow-up after treatment: 5 years (for disease-free survival and overall survival assessments). |

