A study reported at ASCO in 2019 showed that the pCR rate of MSS-type locally advanced rectal cancer patients treated with preoperative long-course concurrent radiotherapy combined with nivolumab (PD-1 inhibitor) reached 30%, and the pCR rate of MSI-H patients reached 60%. A study at the ASCO conference in 2021 reported that 27 cases of rectal cancer received preoperative radiochemotherapy combined with immunotherapy, and the overall pCR rate was as high as 48%, the downstaging rate reached 70%, and the rate of preservation of anus reached 89%. These studies suggest that preoperative radiotherapy combined with immune checkpoint inhibitors can effectively improve the efficacy of rectal cancer radiotherapy and has important clinical application prospects. However, it is still unclear which rectal cancer patients can benefit from radiotherapy combined with immune checkpoint inhibitor treatment, and the biomarkers for treatment benefit and new targets have not yet been clarified, and further research is needed.

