## Inclusion Criteria

Patients must meet all of the following inclusion criteria to be enrolled in the study:

1. Patients voluntarily participate in the study and sign the informed consent form;
2. Age ≥ 18 years and ≤ 80 years;
3. Previously untreated and confirmed by biopsy as rectal adenocarcinoma;
4. MRI shows no distant metastasis, stage II/III (except T4b)
5. The lower edge of the tumor must be within 10 cm of the anal margin;
6. Willing and able to comply with the research protocol;
7. Agree to use blood and tissue samples for research;
8. No history of anti-tumor treatment (such as radiotherapy, chemotherapy, immunotherapy, biology, herbal medicine, etc.);
9. ECOG score 0-2;
10. No immune system diseases (such as systemic lupus erythematosus, rheumatoid arthritis, systemic vasculitis, scleroderma, pemphigus, dermatomyositis, mixed connective tissue disease, autoimmune hemolytic anemia, hyperthyroidism/hypothyroidism, ulcerative colitis, autoimmune hemolytic anemia, HIV infection, etc.);
11. No significant functional impairment of major organs (such as heart, lungs, liver, kidneys, etc.);
12. No jaundice or gastrointestinal obstruction; No acute/chronic infection;
13. No obvious abnormalities in blood routine and biochemical tests: neutrophils≥1.5×109/L, hemoglobin≥80g/L, platelets≥100×109/L, total bilirubin≤1.5×ULN, ALT, AST≤2.5×ULN;
14. No social or mental disorders;
15. For women of childbearing age, the serological pregnancy test result needs to be negative, and effective contraception measures need to be taken within 60 days;

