### Surgery records and pathology assessment

The surgical specimens are preserved and processed according to the operation guidelines for pathological evaluation, and the pathological efficacy is assessed according to the TRG scoring criteria; the degree of radical cure and ypN staging are assessed according to the AJCC Version 8; at least the following information needed to be recorded:

- Length of operation
- Surgical method
- Tumor size
- Tumor site and the distance from the lower edge to the anus
- Number of lymph nodes detected
- Number of lymph node metastases
- Degree of eradication (RX/R0/R1/R2)
- Histological Type
- Microsatellite status (MSS/MSI-L/MSI-H)
- YpTMN staging (AJCC Version 8)
- Residual percentage of viable tumor cells in primary tumor (%)
- Pathologic response grading (TRG Criteria)
- Length of procedure is recorded
- Discharge time after surgery is recorded

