# Statistical analysis of data

## Sample Size

- The primary endpoint is pCR. This study has 80% power to detect an increase in pCR rate from 5% to 20% with a one-sided alpha of 0.05. Considering a 10% drop-out rate, 46 patients will be enrolled.

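### The 5% null is the rate for pMMR/MSS tumours, but the primary test pools patients of any mismatch-repair status, so rejecting 5% could reflect case mix

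*Protocol*

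**What the plan says.** - **Null and its source.** Protocol Summary, Statistical considerations: power is for an increase "from 5% (historical control for pMMR/MSS LARC after standard long-course radiotherapy) to 20% with a one-sided alpha of 0.05". The same entry adds: "Accounting for an anticipated 10% drop-out rate, a total of 30 patients will be enrolled".
- **Restatement.** Section 9.1, Sample Size: "This study has 80% power to detect an increase in pCR rate from 5% to 20% with a one-sided alpha of 0.05". The rates are the same, but the population that the 5% describes is no longer named, and the total given is 46.
- **Eligibility.** The histological requirement is "Previously untreated and confirmed by biopsy as rectal adenocarcinoma", with stage II/III except T4b. Neither the inclusion nor the exclusion criteria, in the Summary or in the body, mention MMR or MSI status.
- **Analysis set.** Section 9.2 makes ITT the primary efficacy set, with no molecular restriction.
- **Evidence that the groups differ.** Under Treatment strategies for rectal cancer, the background describes a conference report of long-course chemoradiotherapy with nivolumab. The pCR rate was 30% in MSS patients, and "the pCR rate of MSI-H patients reached 60"%.
- **Where status is recorded.** Microsatellite status, with MSI-H as one category, is among the items under Surgery records and pathology assessment. It is not in the Screening Period lists.
- **Decision rule.** Section 9.3 describes summaries only. No number of responses that counts as success is stated.

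**The concern.** A single-arm test has no concurrent control, so the fixed null does the control's work and must describe the patients who are tested. Here the null is the rate for one molecular group, while the tested set may contain another group in which the protocol's own background cites twice the pCR under chemoradiotherapy plus PD-1 blockade (60% against 30%).

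The decision turns on about four to six responses. One or two of these from MSI-H patients could move the result across the line with no improvement in pMMR/MSS disease. A reader told that 5% was rejected would take this as a gain over the pMMR/MSS benchmark, and the pooled test cannot separate that from case mix.

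**Working it through.** **Inputs from the protocol.** Null p0 = 0.05 (pMMR/MSS), alternative p1 = 0.20, one-sided alpha 0.05, power 80%, drop-out 10%, N = 30 (Summary) or 46 (section 9.1). MSI-H pCR of 0.60 is the rate in the cited nivolumab study.

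**Assumptions, because the protocol is silent.** The number or share of MSI-H patients; an MSI-H pCR of 0.30 as a lower sensitivity value; and the success cut-off, taken as the smallest r with exact P(X ≥ r | n, 0.05) ≤ 0.05.

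**Step 1: reproduce the plan's figure.** The smallest n with exact alpha ≤ 0.05 and power ≥ 0.80 is 27, with success at 4 or more pCR (alpha 0.0437, power 0.818). Allowing for drop-out, 27 / 0.9 = 30, the Summary's total. The figure of 46 was not reproduced by any of the usual formulas tried. That conflict is a separate matter, so both totals are carried below.

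**Step 2: add MSI-H patients.** With m MSI-H patients whose pCR is q, and n − m pMMR/MSS patients whose pCR stays at 0.05,

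P(positive) = Σ_j P(Bin(m, q) = j) × P(Bin(n − m, 0.05) ≥ r − j).

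Example with n = 27, r = 4, m = 1, q = 0.60: P(Bin(26, 0.05) ≥ 3) = 0.1386 and P(Bin(26, 0.05) ≥ 4) = 0.0387, so P = 0.6 × 0.1386 + 0.4 × 0.0387 = 0.0832 + 0.0155 = 0.0987.

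| Patients analysed, rule | No MSI-H | 1 at 60% | 2 at 60% | 3 at 60% | 2 at 30% |
|---|---|---|---|---|---|
| 27, at least 4 | 4.4% | 9.9% | 19.5% | 33.5% | 10.2% |
| 30, at least 5 | 1.6% | 3.8% | 8.4% | 16.3% | 4.1% |
| 46, at least 6 | 2.6% | 5.3% | 9.9% | 17.0% | 5.5% |

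**Step 3: the same by assumed share f.** The pooled rate is (1 − f) × 0.05 + f × 0.60. For f = 5% this is 0.0475 + 0.0300 = 0.0775.

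| Patients analysed, rule | f = 3% | f = 5% | f = 10% |
|---|---|---|---|
| 27, at least 4 | 10.1% | 15.3% | 31.4% |
| 30, at least 5 | 4.6% | 7.9% | 20.2% |
| 46, at least 6 | 8.3% | 14.3% | 35.2% |

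In both tables, a positive result is false as a statement about pMMR/MSS disease. The pooled rate itself does exceed 5% in these scenarios, which is why the pooled test cannot answer the question set by the benchmark.

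**The case against.** The strongest reply is that the size is not established. No MSI-H share is given, and the larger percentages need a share of about 10% or three patients. The 60% comes from one report with a different PD-1 antibody given with radiotherapy, not after it. The cut-offs are derived, not stated. If all 30 enrolled patients are analysed, as ITT implies, the exact rule is conservative enough to absorb some contamination. All of this stands, and it is why the result is a range and not a single figure.

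Four stronger readings are tempting, and the documents do not support them:

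- *Any MSI-H patient breaks the 5% error rate.* Not so: at 5 or more of 30, one such patient at 60% gives 3.8%, and two at 30% give 4.1%.
- *The protocol assumes 60% pCR in MSI-H patients.* It cites that rate as background and makes no such assumption for sintilimab.
- *The protocol expects MSI-H patients.* It leaves them eligible and provides a field to record the category. That is not a forecast of enrolment.
- *The trial cannot say anything about pMMR/MSS disease.* Microsatellite status is recorded with the surgical pathology, so a pMMR/MSS rate can still be reported. What is missing is a primary test directed at it.

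None of this removes the mismatch, because the null, the eligibility and the primary set are all fixed in this document and do not describe the same patients.

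**Conclusion.** The mismatch is real and should be corrected. As written, a rejection of 5% may come from a handful of MSI-H responders and not from a gain in pMMR/MSS disease.

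If pMMR/MSS pCR is unchanged at 5% and MSI-H pCR is 60%, two MSI-H patients take the false-positive chance above 5% for each number considered: 19.5% at 27, 8.4% at 30 and 9.9% at 46. With one such patient it is 9.9%, 3.8% and 5.3%. If MSI-H pCR is 30%, two such patients give 10.2%, 4.1% and 5.5%, so at 30 the nominal level would still hold. These figures rest on an assumed number of MSI-H patients, one cited study, and cut-offs derived from the stated alpha. They show what can happen, not what will. Severity: should-fix.

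**What to change.** In the Protocol Summary (Statistical considerations), section 9.1 and section 9.2, state that:

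1. The primary test of pCR against 5% is done in ITT patients with pMMR/MSS tumours. pCR in dMMR/MSI-H patients is reported separately and untested, and the pooled rate is descriptive.
2. Status is taken from the existing diagnostic biopsy tissue, with the surgical specimen as back-up. This matters because ITT patients who do not reach surgery would otherwise have no status.
3. Patients of unknown status are counted by a rule set in advance, for example kept in the tested set, with a sensitivity analysis that excludes them.
4. The change is adopted before pCR results by MMR/MSI status are reviewed. The trial is open-label and the Summary gives January 2023 for the first enrolment, so the tested set must not be chosen with those results in view.

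The cost is more than one sentence. MMR/MSI typing is not among the screening tests, so archived biopsies need typing where this has not been done. Without replacement of the patients left out of the test, some power is lost: with success at 4 or more pCR, exact power is 81.8% at n = 27, 79.3% at n = 26 and 76.6% at n = 25. The total need not change if 27 pMMR/MSS patients remain evaluable.

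### The 5% null is stated for pMMR/MSS tumours, but entry and the primary analysis are open to any MMR/MSI status, so the single-arm test may compare a mixed population with an MSS-only benchmark

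*Protocol*

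**What the plan says.** - **Null rate.** Protocol Summary, Statistical considerations: the pCR increase to be detected is from "5% (historical control for pMMR/MSS LARC after standard long-course radiotherapy) to 20% with a one-sided alpha of 0.05". The Sample Size section repeats the rates without naming a population: "This study has 80% power to detect an increase in pCR rate from 5% to 20% with a one-sided alpha of 0.05".
- **Size.** The Summary adds: "Accounting for an anticipated 10% drop-out rate, a total of 30 patients will be enrolled". The Sample Size section gives 46 for the same inputs.
- **Eligibility.** The tumour criterion is "Previously untreated and confirmed by biopsy as rectal adenocarcinoma", with limits on stage and on distance from the anal margin. Neither the inclusion nor the exclusion list, in the Summary or in the body, contains an MMR or MSI condition.
- **Screening.** The Screening Period section lists imaging, endoscopy, pathology and laboratory work, but no MMR/MSI test.
- **Recording.** "Microsatellite status (MSS/MSI-L/MSI-H" appears only in the list under Surgery records and pathology assessment. No source specimen is named for it.
- **Analysis set.** Analysis Population makes ITT primary and defines no pMMR/MSS subset.
- **Background.** Treatment strategies for rectal cancer cites a report on long-course concurrent radiotherapy plus nivolumab. It gives a pCR of 30% in MSS disease and says that "the pCR rate of MSI-H patients reached 60" per cent.

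**The concern.** With one arm, the whole efficacy inference rests on the historical rate. The protocol ties that rate to pMMR/MSS disease, then enrols and analyses patients regardless of status. MSI-H is a category on its own recording list, so it foresees that such patients may be present. Its background also suggests that they respond to this type of treatment about twice as often as MSS patients.

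If some enrolled patients are MSI-H, rejecting the 5% null no longer shows that pCR has improved in the population the 5% describes. A result read against an MSS benchmark could be partly due to patients to whom that benchmark was never said to apply. This is not a detail to leave to an analysis plan, because the null and the eligibility criteria are both fixed in the protocol and do not match.

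A later MSS subset analysis may not repair this. If status is determined on the resection specimen, a pCR specimen offers little or no tumour to test, so there is a risk that status is unknown in some responders.

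**Working it through.** **1. The plan's own figure.** Inputs from the Summary: p0 = 0.05, p1 = 0.20, one-sided alpha 0.05, power 80%, drop-out 10%. By the exact binomial, n = 27 with success at 4 or more pCRs gives
- alpha = P(X ≥ 4 | 27, 0.05) = 0.0437
- power = P(X ≥ 4 | 27, 0.20) = 0.818

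At n = 26 power is 0.793, so 27 is the smallest size that works. Then 27 / 0.9 = 30, which is the Summary's figure. The 46 in the Sample Size section does not follow from these inputs. That is a separate matter, but 46 is carried below because the protocol states it.

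**2. Cut-offs.** The protocol gives none, so they are inferred as the smallest r with P(X ≥ r | n, 0.05) ≤ 0.05.

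| n | r | alpha at r | alpha at r − 1 |
|---|---|---|---|
| 27 (evaluable after drop-out) | 4 | 0.0437 | 0.150 |
| 30 (all enrolled, Summary) | 5 | 0.0156 | 0.061 |
| 46 (all enrolled, Sample Size) | 6 | 0.0263 | 0.079 |

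**3. Stress test.** Let k of the n patients be MSI-H with pCR 0.60 (background figure), and the other n − k be MSS with pCR 0.05 (no benefit). Then

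P(positive) = Σ over j = 0..k of P(Bin(k, 0.60) = j) × P(Bin(n − k, 0.05) ≥ r − j).

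For n = 30, r = 5, k = 2: 0.16 × 0.0117 + 0.48 × 0.0491 + 0.36 × 0.1627 = 0.0019 + 0.0236 + 0.0586 = 0.084.

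For n = 27, r = 4, k = 2: 0.16 × 0.0341 + 0.48 × 0.1271 + 0.36 × 0.3576 = 0.0055 + 0.0610 + 0.1287 = 0.195.

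| Rule | k = 0 | k = 1 | k = 2 | k = 3 |
|---|---|---|---|---|
| ≥5 of 30 | 1.6% | 3.8% | 8.4% | 16.3% |
| ≥4 of 27 | 4.4% | 9.9% | 19.5% | 33.5% |
| ≥6 of 46 | 2.6% | 5.3% | 9.9% | 17.0% |

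**4. Sensitivity to the 60%.** If MSI-H pCR were only 30%, k = 1, 2, 3 would give 2.6, 4.1, 6.2% (30 patients), 6.9, 10.2, 14.5% (27) and 3.9, 5.5, 7.5% (46).

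**5. Sensitivity to the MSI-H share.** The protocol gives no share. For an assumed share f, the overall pCR with no MSS benefit is 0.05 + f × (0.60 − 0.05).

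| Rule | f = 2% | 3% | 5% | 10% |
|---|---|---|---|---|
| ≥5 of 30 | 3.4% | 4.6% | 7.9% | 20.2% |
| ≥4 of 27 | 7.9% | 10.1% | 15.3% | 31.4% |
| ≥6 of 46 | 6.0% | 8.3% | 14.3% | 35.2% |

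**6. Power if MSI-H patients leave the primary test.** With success kept at 4 or more, P(X ≥ r | n, 0.20) is 81.8% at 27, 79.3% at 26 and 76.6% at 25.

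**The case against.** The strongest reply is that the size of the effect depends on quantities the protocol does not fix. It states neither an MSI-H share nor a cut-off. The 60% comes from a conference report on a different PD-1 inhibitor given with radiotherapy, and no denominator is quoted. The same report gives 30% in MSS, so pairing its 60% with an MSS rate of 5% is a stress test and not a forecast. The primary set is ITT, so the rule for all 30 is the natural one. On that rule a single MSI-H patient leaves the error at 3.8%, and an assumed share of 2 to 3% leaves it at 3.4 to 4.6%. All of this stands. It limits the size but does not make the benchmark match the population.

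It can also be said that the stated objective is pCR in locally advanced rectal cancer, and that nothing limits the conclusion to MSS disease. That is correct, and it is why a justified null for the mixed population would also be a cure.

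A reader might infer two stronger points that the documents do not support:

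- **That a few MSI-H responders could carry the trial alone.** One to three such patients yield at most three pCRs, below every cut-off here. Success on MSI-H patients alone needs at least 4 of 27 or 5 of 30 to be MSI-H with that many responding. If exactly that number are enrolled, the chance that all respond is 0.6^4 = 13% or 0.6^5 = 8%. In the scenarios shown, MSI-H responders add to chance MSS responders.
- **That status will be missing in exactly the responders.** The protocol lists the item without requiring the assay on the resection specimen. A diagnostic biopsy is an entry condition, patients agree to research use of tissue, and a further biopsy is planned after chemoradiotherapy. Missing status is therefore a risk only.

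**Conclusion.** The point holds as a mismatch between the null and the population. The 5% is stated for pMMR/MSS disease, while entry, screening and the primary analysis set take no account of MMR/MSI status. Following the protocol as written can therefore lead to a wrong conclusion about the patients to whom the benchmark applies.

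With MSI-H pCR at 60%, two MSI-H patients are enough to push the chance of a positive trial without MSS benefit above 5% under all three rules: 8.4% (30), 19.5% (27) and 9.9% (46). One is enough at 27 (9.9%) and marginally at 46 (5.3%), but not at 30 (3.8%). With MSI-H pCR at 30%, two patients exceed 5% at 27 and 46 but not at 30.

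It would be too strong to say that the 5% error rate fails in every case: with all 30 counted and at most one MSI-H patient, it does not. The mismatch is certain from the text. Its size rests on an assumed MSI-H count, a response rate carried over from another drug, and inferred cut-offs.

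**What to change.** 1. Determine and record MMR/MSI status from the pre-treatment diagnostic biopsy, and name that specimen in the protocol.
2. Run the primary test against 5% in patients who are pMMR/MSS on that biopsy, and report dMMR/MSI-H patients separately. Two alternatives are to add pMMR/MSS to the inclusion criteria, or to keep the mixed population and justify a null rate for it.
3. State the responder cut-off and the number of patients to which it applies, and reconcile the 30 and the 46.

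**Cost.** The biopsy already exists and status is already an item to be recorded, so the added work is an MMR/MSI result for each patient at entry. The statistical cost is power. Taking one MSI-H patient out of 27 lowers it from 81.8% to 79.3%, and taking out two lowers it to 76.6%. Either restate the power, or count the planned number in pMMR/MSS patients only: 27 evaluable and 27 / 0.9 = 30 enrolled, with an exact error of 4.4%. If enrolment is already complete, the analysis-set change is still possible wherever pre-treatment status or tissue is available.
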